### Outcomes {12}

#### Primary endpoint

The primary endpoint is IgE-mediated food allergy to the target food (hen’s egg, cow’s milk, peanuts, or hazelnuts), after 3–6 months of intervention (plus max. 3 months in case of postponed oral food challenge). For polyvalent-sensitized children, a “primary target food allergen” will be determined randomly at enrollment which will be used to define the primary endpoint.

The presence of IgE-mediated food allergy is defined by either of the following (Table 2):Positive oral food challenge (plus sIgE ≥ 0.1 or positive skin prick test)An immediate-type allergic reaction due to an accidental exposure (plus sIgE ≥ 0.1 or positive skin prick test)

**Table 2 Tab2:** Diagnosis of food allergy for the determination of endpoints

Procedure	Positive result
**Oral food challenge (OFC)**	OFC outcome is positive if objective symptoms of immediate type allergic reactions occur after any administered dose. (OFC outcome is negative if no objective symptoms of immediate type allergic reactions occur after ingestion of any administered dose.)
**Allergen-specific IgE (sIgE)**	sIgE ≥ 0.1 kU/l
**Skin prick test (SPT)**	Wheel size ≥ 3 mm
**Immediate-type allergic reaction due to accidental exposure**	Parent-reported objective symptoms of immediate type allergic reactions upon accidental exposure to the interventional food(s) during the interventional period

OFC, sIgE determination (blood sampling), and skin prick test (SPT) are performed onsite on the day of the scheduled visit (V2), which should be 3–6 months (plus max. 3 months in case of postponed oral food challenge) after the start of the intervention (V1). Specific IgE and/or SPT at baseline must be assessed no longer than 3 months prior to enrollment.

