## Statistical methods

### Statistical methods for primary and secondary outcomes {20a}

The primary analysis of the primary endpoint will be performed by logistic regression with (fixed) factor treatment group (verum, placebo regarding the primary allergen) and the stratification factors primary allergen (hen’s egg, cow’s milk, peanuts, hazelnuts), age group (≤ 2, > 2 years of age), grade of sensitization (low, medium, and high), and planned duration of intervention (< 5, ≥ 5 months). In case of stratification groups with very few cases, stratification groups may be combined (e.g., low vs. medium/high grade of sensitization) or the factor omitted from the analysis model; the decision will be finalized, blinded, and described in the statistical analysis plan (SAP). From this model, the odds ratio for verum vs. placebo treatment will be calculated with a 95% confidence interval and a *p*-value for the treatment group comparison. The analysis will be performed on the full analysis set (FAS) based on the intention-to-treat principle without imputation of missing values. The significance level will be set to 0.05 (two-sided). All other analyses will be considered explorative. Several explorative sensitivity analyses will be performed for the primary endpoint: a re-run of the primary analysis model with the per-protocol population (instead of the FAS). In case of relevant differences between the treatment groups with respect to baseline variables, the primary analysis will be repeated with further adjustment variables (FAS population). To account for the potentially varying lengths of follow-up, a Cox proportional hazards regression as well as Poisson regression will be used to analyze the primary endpoint. Explorative analysis of secondary endpoints will follow the same principle as the primary analysis of the primary endpoint, i.e., models with the (fixed) factor treatment group and the stratification factors. Binary endpoints will be analyzed by logistic regression; continuous endpoints will be analyzed by analysis of covariance (ANCOVA) with the respective baseline value (if available) as an additional covariate. Secondary endpoints will be analyzed with the FAS. Regarding safety endpoints, the nature, frequency, and severity of adverse events and safety variables, including serious adverse events, will be summarized descriptively by treatment group (based on the safety population of all participants who received at least one dose of study treatment and have at least one post-baseline safety assessment, analyzed according to the treatment received). Further details will be described in the SAP, which will be finalized prior to data analysis.

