### Methods in analysis to handle protocol non-adherence and any statistical methods to handle missing data {20c}

Selected secondary endpoints will also be analyzed with the per-protocol (PP) population. The PP is a subset of the FAS defined without participants with repeated insufficient consumption of the study product (verum), i.e., consumption < 3 times/week for 3 weeks (either during 3 consecutive weeks or three repeated events of 1 week); OFC taking place before 3 months (after starting the intervention); or OFC taking place after more than 9 months (after starting the intervention). As a general strategy, missing data will not be imputed in this study.

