#### Adverse event reporting and harms {22}

Pre-existing diseases will be recorded in the subject’s file and in the eCRF system under medical and/or allergy history. Subject reported or physician confirmed worsening of these conditions, or a change of prescribed medication will be assessed during the study visit/phone call and documented in the subject’s file/source data. However, worsening of pre-existing diseases will not be considered as AEs, except those categorized as AEs of special interest (AEIs).

For this specific protocol, AEIs include immediate-type allergic reaction after food exposure, worsening of eczema (in case of eczema), and defined gastrointestinal (GI) symptoms (abdominal pain, bloating, vomiting, difficulties swallowing, stool irregularities).

An accidental food allergen exposure is any known or suspected exposure to a food to which the subject is allergic or sensitized without known clinical relevance, whether or not it results in an AEI.

A serious adverse event (SAE) or serious adverse reaction is defined as any untoward medical occurrence that leads to death, is life-threatening, requires inpatient hospitalization (longer than 24 h), or prolongs an existing hospitalization or results in persistent or significant disability or incapacity. Excluded from this definition are hospitalizations as treatments of a pre-existing condition planned before inclusion into the study or elective surgeries, planned before inclusion into or during the study. According to the seriousness grading, the investigators will review each AE. If the criteria for a SAE are met, the clinical research site will follow local procedures according to the GCP guidelines. All expected and unexpected serious adverse events occurring after the subject’s parents/caregivers have signed the informed consent and the intervention has been started must be reported on a SAE form to the study principal investigator within 24 h of becoming aware of the event.

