Any serious allergic reaction related to the study intervention will lead to a temporary halt of the study in order to re-evaluate the safety conditions. For this purpose, an external safety advisory board is called in to advise the PI and the CO-PI of the study. Based on the recommendations of this committee, a decision is made as to whether the study can be continued or whether changes to the design need to be made. If three participants experience serious allergic reactions related to the study intervention, the study will be stopped.

AE/AEI recording will extend from enrollment until the end of the study at V2.

Parents of the participants should document all AEs and AEIs occurring during the study in the subject’s (e-)diary. Moreover, the subject’s parents will be instructed to document accidental food allergen exposures in detail in the (e-)diary and to contact the study site after any known or suspected food allergen exposure, even if it does not cause symptoms. In case of an immediate type allergic reaction after food exposure (either to the study product or due to exposure to (other) food allergens) or recurrent GI symptoms, parents of the participants are asked to call the study site. During the phone call and the second study visit, the subject’s parents/caregivers will be queried on AEs/AEIs based on the patient’s diary and changes in the subject’s condition.

For this specific protocol, only AEIs (see above) and SAEs are logged as (S)AEs in the eCRF. Information will be recorded regarding the date of onset, date of resolution, seriousness, severity, outcome, treatment required, causality, action taken with the study intervention if applicable, possible augmentation factors, and/or other possible causes. For scoring the severity of immediate-type allergic reactions, the grading system for food-induced anaphylaxis published by Sampson is used [14].

The investigators will assess the causality/relationship between the study intervention and the AE. Causality will be documented as related or not related to the intake of the study intervention. Overall, the occurrence of immediate type allergic reactions within 2–3 h after food allergen exposure (study intervention and/or accidental exposure) will be considered as related to food exposure.

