However, besides the timing of introduction and the target group (children at risk versus children from the general population), the amount and the preparation of allergens as well as the duration and frequency of intake may play a role regarding food allergy prevention. Concerning hen’s egg, several interventional studies using pasteurized raw hen’s egg with amounts ranging from 350 mg to 2.5 g showed no significant reduction of hen’s egg allergy due to an early introduction, but high rates of adverse reactions, both immediate type symptoms and gastrointestinal problems [20–22]. In contrast, the PETIT study using small amounts (25 mg for 3 months, then 125 mg for 3 months) of baked hen’s egg could show an effect on the prevention of hen’s egg allergy [6]. Within the LEAP trial, relatively high amounts of peanut protein were administered (6 g per week, distributed in three or more meals), but no major safety issues occurred [7]. Nevertheless, it has to be mentioned that a SPT with peanuts was performed prior to randomization, and infants with a wheal size greater than 4 mm were not randomized [7]. Considering that in the TIFFANI trial, also children with high sIgE levels at baseline will be enrolled, very small amounts of food allergens are used, reflecting the allergen-specific reference doses “ED_05_” (approximately 2 mg food protein of hen’s egg, cow’s milk, hazelnuts, and peanuts). The ED_05_ is defined as the eliciting dose at which 5% of the respective allergic population would be predicted to experience an allergic reaction [23].

Regarding the duration of the intervention, most randomized-controlled studies investigating the effect of an early introduction of food allergens on the development of food allergy, have decided on an interventional period of 6 months or longer. Within the SPADE study, however, two OFCs were performed to examine the preventive effect of an early introduction of small amounts of cow’s milk formula in breast-fed infants from the general population after approximately 2 and 5 months of intervention [24]. After 5 months of intervention, 0.8% of the ingestion group versus 6.8% of the placebo group developed cow’s milk allergy. But interestingly, even after only approximately 2 months of intervention there was a tendency towards a preventive effect of an early cow’s milk introduction (0.4% suffered from cow’s milk allergy in the ingestion group, compared to 2.5% in the avoidance group) [24].

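### An objective reaction to the study powder is not an endpoint event, and missing outcomes are not imputed, so active-arm children who react and have no food challenge leave the primary analysis

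*Protocol article*

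**What the plan says.** Under Primary endpoint, food allergy is established by a positive OFC or by "An immediate-type allergic reaction due to an accidental exposure (plus sIgE ≥ 0.1 or positive skin prick test"). Table 2 words this second route as "Parent-reported objective symptoms of immediate type allergic reactions upon accidental exposure to the interventional food(s) during the interventional period". The assigned study powder is not mentioned in either place.

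Adverse event reporting and harms {22} uses the terms in two ways. Its definition is broad: "An accidental food allergen exposure is any known or suspected exposure to a food to which the subject is allergic or sensitized". Later the same section separates the sources. Parents are to call after an immediate reaction, "either to the study product or due to exposure to (other) food allergens", and causality is judged after "food allergen exposure (study intervention and/or accidental exposure").

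For the analysis, section {20a} says: "The analysis will be performed on the full analysis set (FAS) based on the intention-to-treat principle without imputation of missing values". Section {20c} repeats: "As a general strategy, missing data will not be imputed in this study". The sensitivity analyses named for the primary endpoint are a per-protocol re-run, extra baseline covariates, Cox regression and Poisson regression.

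Section {18b} encourages families to keep their visits after the intervention is discontinued.

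**The concern.** The endpoint gives no status to the most direct sign of allergy that the trial can produce before visit 2. The powder delivers 1.7 to 2.0 mg of protein (Table 1). The OFC starts at approximately 2 mg ({18a}) and is positive if objective symptoms follow any dose (Table 2). An objective reaction to about 2 mg therefore counts at the challenge, and counts if the food was eaten by accident, but does not count if it came from the powder.

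This does no harm while the child goes on to an OFC. If the child does not, the outcome is missing, and with no imputation the child cannot enter the logistic regression. Placebo powder contains none of the four allergens, so the mechanism works in the active arm only and removes only children who have shown an allergic reaction. At stake is a one-directional bias in the single confirmatory comparison.

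**Working it through.** **Inputs from the article.** 69 children per arm randomised, 62 per arm analysed, 35% vs 60% food allergy, two-sided 5% chi-squared test, 80% power, about 10% dropout (Sample size {14}). ED05 is the "eliciting dose at which 5% of the respective allergic population would be predicted to experience an allergic reaction" (Discussion).

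**Step 1: the plan's own figure.** With pooled proportion 0.475 and no continuity correction, n per arm = [1.96·√(2·0.475·0.525) + 0.8416·√(0.35·0.65 + 0.60·0.40)]² / 0.25² = 61.4, so 62. Power at 62 per arm is 80.4%, and 124/0.9 = 137.8, so 138. The sample size reproduces and is not in dispute.

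**Step 2: which children are lost.**

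| Child in the active arm | Outcome under the stated rules |
|---|---|
| Reacts to powder, has OFC | OFC result; stays in the model |
| Reacts to accidental exposure, no OFC | Allergic; stays in the model |
| Reacts to powder, no OFC, no accidental reaction | None; leaves the model |

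Only the third row is affected. The listed sensitivity analyses do not repair it. The per-protocol set is a subset of the full analysis set. Extra covariates, Cox and Poisson are applied to the same endpoint. Cox could keep the child as censored, but the reaction would still not count.

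**Step 3: how many reactors.** Reading ED05 as a 5% chance per allergic child at one dose, expected active-arm reactors are 69 × 0.60 × 0.05 = 2.1 if 60% are allergic and 69 × 0.35 × 0.05 = 1.2 if 35% are. This treats the trial children as the ED05 reference population and ignores repeated daily dosing. It counts reactors, not reactors without an OFC. The article gives no figure for the latter, so k below is an assumption.

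**Step 4: size under no true effect.** Both arms have a true rate of 60%, 69 per arm, with no other losses. Removing k allergic active children gives an observed active rate of (41.4 − k)/(69 − k), and OR = [rate/(1 − rate)]/(0.60/0.40). For k = 2: 39.4/67 = 58.8%, OR 0.95. For k = 7: 34.4/62 = 55.5%, OR 0.83.

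The last column is the chance of a significant result favouring verum. It comes from exact binomial enumeration of the uncorrected chi-squared test, with the number lost random and k its mean. It approximates the planned adjusted logistic regression.

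| k lost | Active rate | OR | False positive favouring verum |
|---|---|---|---|
| 0 | 60.0% | 1.00 | 2.4% |
| 2 | 58.8% | 0.95 | 3.6% |
| 3 | 58.2% | 0.93 | 4.2% |
| 5 | 56.9% | 0.88 | 5.6% |
| 7 | 55.5% | 0.83 | 7.6% |

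Seven is 69 − 62, the whole dropout allowed for in the active arm.

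**Step 5: size at the design rates.** If the true active rate is 35%, the observed rate is (24.15 − k)/(69 − k). The OR is 0.36 with none lost, 0.33 with 2 lost (22.15/67 = 33.1%) and 0.26 with 7 lost (17.15/62 = 27.7%, OR 0.255).

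**The case against.** The strongest reply is that the loss is conditional and probably small. The OFC is already scheduled for routine diagnostics when the child is enrolled (section {10}), and families are encouraged to attend after stopping the product. Section {11b} allows stopping of the one product concerned. The article nowhere says that reactors decline the OFC. All of this stands. If one of two reactors skips the OFC, the null appears as 40.4/68 = 59.4%, OR 0.98.

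A second reply is that the broad definition of accidental exposure could be read to include the powder. But a scheduled daily feeding is hard to call accidental, and the same section lists the study intervention and accidental exposure as different sources. At best, the confirmatory endpoint is open to two readings.

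A third reply is that missing-data sensitivity analyses belong in the statistical analysis plan, which is not shown. That is fair, and their absence from the article is not part of this point. The endpoint definition and the no-imputation rule, however, are fixed in the article.

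A reader might infer more than the documents support:
- **That many children vanish, say eight or more.** Eight exceeds the roughly seven dropouts planned for the active arm, and the ED05 gives one or two reactors at a single dose.
- **That a worst case shows the size of this problem**, with every missing active child allergic and every missing placebo child not. That would test about 10% missing data in general. This mechanism says nothing about placebo dropouts.
- **That 124 of 138 is an exclusion rule.** It is a dropout allowance, and the article does not define membership of the full analysis set.

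**Conclusion.** The point holds in limited form. As written, a child who reacts to the active powder and has no evaluable OFC or accidental reaction has no primary outcome and leaves an analysis described as intention-to-treat. The direction is certain: towards verum. The size is not. At the article's own single-dose figure the bias is small (OR 0.95 under no effect if two such children are lost). It becomes material only if months of daily dosing, or refusals after a reaction, push the count towards the full planned dropout (OR 0.83, false-positive rate 7.6%). These figures assume that every lost child is allergic and that nothing else is missing.

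The documents do not support calling the planned primary analysis unusable or replacing it. They support closing a gap in the endpoint definition before unblinding.

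**What to change.** 1. **Endpoint rule, fixed before unblinding.** Under Primary endpoint and in Table 2, state that an objective immediate reaction to the powder of the primary target food, with sIgE ≥ 0.1 kU/l or a positive skin prick test, counts as food allergy when no evaluable OFC exists. Where an OFC is done, its result decides. Judge it blinded and by the same rule in both arms. Say which sIgE or skin test applies when visit 2 is missed; the baseline value is available for every enrolled child. Letting the OFC decide treats powder reactions differently from accidental ones. The reason is that only active children meet the allergen in the powder daily, so counting every powder reaction would tilt the comparison the other way.
2. **Definitions.** Reconcile the broad definition of accidental exposure in section {22} with the later wording that separates it from the study product.
3. **Analysis.** Keep the planned logistic regression as primary. Add a sensitivity analysis of all randomised children: multiple imputation using the stratification factors, sIgE and skin test, consumption and reactions, plus a tipping-point analysis for missing active-arm outcomes.

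**Cost.** A few sentences and some extra analysis on data already recorded, since immediate reactions are logged as adverse events of special interest. The estimate may be less favourable. If 35% holds among 62 active completers and reactors are added as allergic, the active rate is (21.7 + k)/(62 + k). Two added reactors give 23.7/64 = 37.0% and power of 73.8% instead of 80.4%; seven give 28.7/69 = 41.6% and 55.8%. If the planned 35% was meant to include such children, this loss does not arise.

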**Methods:**

In this randomized, placebo-controlled, double-blind, single-center trial, 138 children (8 months to 4 years of age) sensitized to the target allergen(s) hen’s egg, cow’s milk, peanuts, and/or hazelnuts with unknown clinical relevance will be randomized in a 1:1 ratio to either an active or a placebo group, daily receiving a rusk-like biscuit powder with or without the target allergen(s) for 3–6 months until an OFC will be performed in routine diagnostics. The primary endpoint is an IgE-mediated food allergy to the primary target allergen, after the interventional period.

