	**Interventional allergens**			
	**Peanut**	**Hazelnut**	**Hen’s egg**	**Cow’s milk**
**Amount of protein [mg/3 g] to be taken once daily**	1.7	1.9	1.8	2.0

The sugar-free, rusk-like biscuit powder (3 g of powder/day using a measuring spoon) will be mixed with water, and optionally fruits, to a puree. The study product should be eaten daily throughout the study duration. The first feeding of the study product at visit 1 (V1) will be performed under medical supervision at the study center. The duration of the intervention is determined by the date of the routinely scheduled OFC at visit 2 (V2) and should be at least 3 months and up to 6 months after inclusion to the trial. In case of a postponed OFC (e.g., due to illness of the child), the duration of the intervention can be extended up to a maximum of 9 months.

In the placebo group, subjects consume daily the same sugar-free rusk-like biscuit powder, however, without cow’s milk, hen’s egg, peanuts, or hazelnuts following the same instructions as the active group. To ensure blinding, the first feeding of the placebo study product will also be performed under medical supervision at the study site.

In infants, first, weaning foods (e.g., vegetables) should have been successfully introduced for at least 1 week before feeding the study product. Mothers will be encouraged to continue breastfeeding while introducing weaning foods. Parents of both groups will be advised to avoid cow’s milk, hen’s egg, peanuts, hazelnuts, or their products in their child’s diet according to the individual sensitization profile.

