#### Sample size {14}

A total of 138 children are planned to be included in the trial. Analyzing 124 children (62 in each group) will result in at least 80% power assuming a difference in the primary endpoint (food allergy after 3–6 months (plus max. 3 months) of 35% in the active group vs. 60% in the control group, based on a two-sided chi-squared test with significance level 5% (two-sided). To compensate for a potential dropout rate of about 10%, 138 infants will be randomized (69 children in each group). Sample size calculation was performed in SAS for Windows version 9.4 (SAS Institute, Cary, NC, USA).

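### For allergy found at the food challenge, the planned Cox analysis can only use the appointment date as event time: it does not adjust for follow-up and loses about 30 points of power, and the Poisson model needs its offset and variance fixed

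*Protocol article*

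**What the plan says.** The primary analysis in Statistical methods {20a} is a logistic regression adjusted for the stratification factors, planned duration (<5 or ≥5 months) among them. The same section lists exploratory sensitivity analyses. To deal with follow-up of differing length, "a Cox proportional hazards regression as well as Poisson regression will be used to analyze the primary endpoint". It names no time variable, offset or variance estimator, and leaves further detail to the SAP.

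The length of follow-up is set by the clinic's calendar. The intervention description says: "The duration of the intervention is determined by the date of the routinely scheduled OFC at visit 2 (V2"). It should be 3 to 6 months, with an extension to at most 9 if the challenge is postponed.

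The Primary endpoint section has two routes to a positive outcome, each needing sIgE or skin prick confirmation. The first is a positive challenge, for which "OFC, sIgE determination (blood sampling), and skin prick test (SPT) are performed onsite on the day of the scheduled visit (V2"). The second is a parent-reported immediate reaction to accidental exposure during the intervention. For logged reactions the eCRF takes a date of onset (Adverse event reporting {22}).

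**The concern.** Cox regression needs the time at which the event happened. For a child who is positive at challenge, the only time available is the appointment date. Allergy may have begun at any point before it, so these are current-status data: one reading, at one externally chosen time.

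Using that date as an event time has two consequences. Each positive child is compared with children not yet challenged, who count as event-free although their status is simply unread. And the modelled hazard is the rate at which challenges take place multiplied by the proportion positive, so it mixes scheduling with allergy and does not remove the effect of unequal follow-up.

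A Poisson model with log time as offset has a related fault. It makes the expected proportion positive at 6 months twice that at 3 months, and nothing in the protocol supports such proportionality.

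At stake is how a positive trial would be read. These two models are meant to show that the result does not depend on varying follow-up. If they often miss significance when the primary analysis does not, a true effect may look fragile for reasons unrelated to follow-up.

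**Working it through.** **Inputs from Sample size {14}.** Rates "35% in the active group vs. 60% in the control group"; "Analyzing 124 children (62 in each group) will result in at least 80% power"; "based on a two-sided chi-squared test with significance level 5% (two-sided"). Dropout is about 10%, with 138 randomised.

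**The plan's own figure.**
- Per arm, with mean rate 0.475: n = [1.96·√(2·0.475·0.525) + 0.8416·√(0.35·0.65 + 0.60·0.40)]² / 0.25² = (1.384 + 0.575)² / 0.0625 ≈ 61.4, so 62.
- Power at 62 per arm is 0.804, and 124/0.9 = 137.8, so 138.
- The plan's figures reproduce.

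**Closed form at the design rates.** Expected positives are 62·0.35 = 21.7 and 62·0.60 = 37.2, total 58.9. The log risk ratio is ln(0.35/0.60) = −0.539.
- Poisson, model-based SE: √(1/21.7 + 1/37.2) = 0.270. Power = Φ(0.539/0.270 − 1.96) ≈ 0.51.
- Binomial SE, which robust variance estimates: √(0.65/21.7 + 0.40/37.2) = 0.202. Power = Φ(0.539/0.202 − 1.96) ≈ 0.76.
- Ratio 0.270/0.202 = 1.34, so the model-based SE is 34% too wide.
- Cox by the Schoenfeld formula, HR 0.583: Φ(0.539·√(58.9/4) − 1.96) = Φ(0.108) = 0.54.

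**Simulation.** 62 per arm, 6,000 trials per scenario, treatment as the only covariate. Assumed: OFC dates uniform over 3-6 months, 10% postponed to 6-9 months, and the same distribution in both arms. The protocol gives neither the date distribution nor the share of accidental reactions. The Poisson columns use a log-time offset.

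| Scenario, 35% vs 60% | Logistic | Cox | Poisson, model SE | Poisson, robust SE |
|---|---|---|---|---|
| Status unrelated to OFC date | 0.829 | 0.509 | 0.527 | 0.777 |
| Risk accruing with time | 0.808 | 0.482 | 0.504 | 0.782 |
| Row 1, 10% of positives dated accidental reactions | 0.824 | 0.533 | 0.547 | 0.760 |
| Row 1, 30% dated | 0.829 | 0.595 | 0.594 | 0.765 |

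- **Cox loss:** 0.829 − 0.509 = 0.320 and 0.808 − 0.482 = 0.326 with no dated reactions; 0.829 − 0.595 = 0.234 with 30% dated.
- **Poisson loss, robust SE:** between 0.808 − 0.782 = 0.026 and 0.829 − 0.765 = 0.064.
- **Poisson model-based SE against the empirical SD:** 28% and 32% too wide in rows 1 and 2. With 15% postponed instead of 10%, a separate simulation gives 0.273/0.217, or 26%. With the closed form, the range is 26-34%.
- **Equal rates in both arms (35%, 47.5%, 60%):** Cox rejects in 4.9-5.3% of trials, model-based Poisson in 0.2-1.3%. The Cox SE matches its empirical SD (ratio 0.98-1.00).

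The Cox loss is therefore one of precision, not a wrong standard error. The order of appointments, which is noise with respect to allergy, enters the estimate.

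**The alternative.** In a separate simulation at the design rates, logistic regression had power 0.81 and logistic regression plus the actual interval 0.79, against 0.48 for Cox.

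**The case against.** The strongest reply has four parts.

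1. *The details belong to the SAP.* This stands for Poisson. Modified Poisson with robust variance and no offset is one permissible reading of the present wording. A reader might infer that both models necessarily lose about 30 points, or that Poisson standard errors will be too wide. The protocol does not support that, because it fixes no variance estimator. It does not rescue Cox, which is named outright and has no other clock for challenge-diagnosed children.

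2. *The endpoint does contain event times.* This stands in part. Accidental-exposure reactions have real dates, so the criticism applies to the challenge component. The protocol gives no expected share; at 30% the Cox loss is still about 23 points.

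3. *Cox is not invalid.* This stands as simulated: type I error is held when OFC dates are distributed alike in both arms. A reader might infer that Cox would give false positives; the calculations do not show that.

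4. *Duration is already handled, and these analyses are exploratory.* Largely true. Planned duration is a stratification factor and a primary-model term, and {20b} plans a duration-by-treatment interaction. What is missing is a sensitivity analysis that uses the actual interval correctly.

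A reader might also infer that many children are assumed to be allergic at entry. The protocol says only that clinical relevance is unknown. The point does not need that premise: it is enough that the challenge date is not an onset date.

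**Conclusion.** The point holds with limits. For the challenge component, the Cox analysis does not do the job stated for it, and neither does a Poisson model if it carries a log-time offset. Cox power at the design rates is about 0.48-0.51 against about 0.81 for logistic regression. The Poisson penalty is conditional: an SE about 26-34% too wide and power about 0.50 with model-based variance, but a loss of only about 3-6 points with robust variance.

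These sizes rest on the assumed OFC dates, on no covariates other than treatment, and on few dated accidental reactions.

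A reader might infer that the trial's main conclusion is at risk. It is not: the confirmatory logistic test and the sample size are untouched. The consequence is one of interpretation. At the assumed effect, Cox would miss significance in about half of trials, against about one in five for the primary model, so a true positive could look non-robust. The change should be made, but it is not critical.

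**What to change.** In the SAP:

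1. Replace Cox on the OFC date with the primary logistic model plus the actual V1-to-OFC interval as a continuous covariate. For children with an accidental reaction, use the interval to the V2 assessment, not to the reaction. If a hazard-type estimate is wanted, use a current-status model instead: binary regression with a complementary log-log link and a term for time. The actual interval arises after randomisation, since postponement could be related to treatment, so keep this as a sensitivity analysis beside the planned-duration factor.
2. Specify Poisson as modified Poisson: log link, robust variance, no time offset, reported as a risk ratio.
3. Add no new duration interaction; {20b} already has one.

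The cost is a few lines of SAP text before it is finalised. The V1 and V2 dates are already recorded, and no new data or software are needed.
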